### Procedure for unblinding if needed {17b}

There is no blinding of study personnel, so unblinding is not necessary. After the “last patient in” completes the study, we will debrief participants in the simulated personalization group that they did not receive a personalized treatment.

## Data collection and management

### Plans for assessment and collection of outcomes {18a}

Our primary outcome is depressive symptoms, with secondary measures including anxiety state/trait, treatment discontinuation, adherence, usability, and negative effects. Other measures encompass sociodemographic, clinical, and psychotherapy mechanism-related variables. Outcomes will be self-reported at baseline (t_0_), mid-treatment 3 weeks after allocation (t_3_), post-treatment 6 weeks after allocation (t_6_), and at 12 weeks (t_7_) post-allocation. A shorter assessment battery of depression and psychotherapy mechanisms will be assessed weekly. All questionnaires will be collected in the DIRECT app. In case of low response rates to the questionnaires, we may contact participants via telephone to encourage completion of assessments in the app. We will also conduct qualitative interviews post-treatment with a subsample of participants to gather their experiences in the IMI and their subjective perceptions of the assumed change mechanisms. Table 2 provides a detailed overview of all assessments.

### Plans to promote participant retention and complete follow-up {18b}

The DIRECT app will automatically notify participants with push notifications that assessments are available to be completed in the app. Also, we will send reminders for mid-, post-, and follow-up assessments if participants do not complete these assessments approximately two days after availability as well as five days after availability. We will offer a monetary incentive to complete the assessments: participants will receive a €45 gift voucher for completing all assessments (mid-, post-, and follow-up). We will continue to invite participants to assessments, even if they have not continued to work with the app.

### Data management {19}

Except for the qualitative interviews, all data is gathered online and will be recorded automatically by the DIRECT app. Data will be stored on a secure server (see “Confidentiality {27}”). After completion of the study, de-identified data will be made publicly available in an Open Science Framework (OSF) repository. De-identified data will also be shared with the overarching project of the TRR/CRC 289 via a secure platform.

### Confidentiality {27}

When participants register in the DIRECT app, they provide their email address and telephone number. Participants use the email to log in, receive assessment reminders, and recover their accounts. The telephone number will enable the study team to contact participants in case of suicidal ideation/crises and for the scheduled mid-treatment telephone call. In case of low response rates to the assessments, participants may also be contacted via telephone to encourage completion of questionnaires on the platform. Data will be stored on a secure server. Different roles within the study team will ensure that only select personnel can access personal information. Personal information and questionnaire data will be stored in separate databases. The data is saved locally on the participant's smartphone. The login password as well as any other safety measures participants use on their own device ensures data. Synchronization of the local data will be achieved through encrypted (SSL) data transfer to a server located in Germany. The server is provided by Hetzner GmbH, an ISO 27001 hosting provider that complies with the EU General Data Protection Regulation (GDPR). Synchronization to the server and storage is required to ensure that the study team can support participants. The study team can access the admin panel through two-factor authentication. Data export is also protected by two-factor authentication and can only be achieved by the role of the study coordinators. Exported data is pseudonymized by assigning an internal ID (hash). Personal data is not exported. Study IDs and personal data are not matched outside of the admin panel. Following GDPR regulations, participants can delete their own data and we will also delete data upon request by participants. Upon completion of the trial, we will export all data and store it on an encrypted device for 10 years in accordance with good practice guidelines for clinical trials. After completion of the study and data analysis, all data from the app and the servers will be deleted. We will inform participants about what data is assessed, how it is transferred, and where and how long it is stored before they provide informed consent.

### Plans for collection, laboratory evaluation and storage of biological specimens for genetic or molecular analysis in this trial/future use {33}

N/a: We will not collect biological specimens.

## Statistical methods

### Statistical methods for primary and secondary outcomes {20a}

The planned analysis is described below. We will publish an updated statistical analysis plan before analyzing the research report for research question 1. This plan will take into account any issues that cannot be predicted at this stage but may emerge during the conduct of the trials (e.g., higher rates of people not receiving the intervention as planned).

Main Research Question 1: *How do simulated personalization before treatment and expectation-optimized personal contact 3 weeks after treatment initiation modulate treatment effects (e.g., the difference in depressive symptom load and secondary outcome measures at 3, 6, and 12 weeks after randomization) and treatment discontinuation?*

We assess the differences in depressive symptom load 3, 6, and 12 weeks after randomization. We treat the BDI-II score as a continuous variable. We will use factorial ANCOVA models. To explore the difference in depressive symptoms 3 weeks after treatment initiation, we use simulated personalization (F1) as the independent variable. For week 6 and 12, we use mid-treatment expectations focused contact (F2), as well as the interaction between F1 and F2 as independent variables. All ANCOVA models will include age and baseline symptom severity as covariates. We will report marginal means for each factor level of the main factors and means for each treatment arm. Pairwise comparisons between factor levels corrected for multiplicity will be reported. We will apply the same method for all other continuous secondary outcome measures available at the respective measurement occasions. We will report the difference in means in units of the scale score. Cohen’s *d*-like effect sizes will be reported. Effects on treatment discontinuation will be inspected using a rank-based test for factorial designs. Differences in rates, as well as relative effects, will be reported.

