### Objectives {7}

We postulate that (simulated) personalization before initiating an IMI and an expectation-optimizing personal contact at mid-treatment would modify patients’ expectations and improve treatment effects. A factorial design will enable us to disentangle the mechanisms and effects of two important modulators of outcome expectations (i.e., personalization and personal contact) and, importantly, their temporal dynamics and interaction with person- and depression-related factors.

The objectives are:To determine whether framing the IMI as personalized enhances initial expectations and amplifies treatment effects compared to standard framing.To determine whether expectation-optimizing personal contact amplifies treatment effects. Here, we will also disentangle whether this effect is due to the specific quality of this contact or the non-specific, “common” factors of personal contact by comparing the expectation-optimizing contact to non-specific contact and no-contact conditions.To explore which variables moderate (e.g., do patients with low expectations benefit more from an expectation-optimizing personal contact?) and/or mediate (e.g., therapeutic alliance, self-efficacy) the effects of the expectation-optimizing strategies.To investigate the trajectories of depression, positive and negative expectations, and other relevant treatment factors over time.

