## Interventions

### Explanation for the choice of comparators {6b}

This 2 (intervention framing pre-treatment: simulated personalization vs. standard framing) × 3 (telephone contact mid-treatment: no contact vs. non-specific contact vs. expectation-optimizing contact) factorial randomized controlled trial will examine two randomization factors (framing pre-treatment and personal contact mid-treatment). The comparison is conducted between the treatment arms, considering the potential interaction between the treatment factors.

The first randomization factor concerns the framing of the intervention: Patients will either receive the intervention in the standard framing or receive the same intervention with a personalized framing, simulating that the intervention is tailored to them according to their baseline data. The second randomization factor concerns a personal contact at mid-treatment: Patients will either receive a personal contact session focused on expectations, a supportive personal contact session not focused on expectations, or no personal contact. Thus, we will determine whether modulating outcome expectations by simulating personalization and personal contact at mid-treatment contributes to the treatment outcome at 3, 6, and 12 weeks after randomization.

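### The week 6 and week 12 ANCOVA is written without the framing (F1) main effect, so what the model tests depends on an unstated coding

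*Protocol article*

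**What the plan says.** The section on statistical methods for primary and secondary outcomes {20a} names the model class ("We will use factorial ANCOVA models") and then lists the terms by time point.

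- Week 3: "To explore the difference in depressive symptoms 3 weeks after treatment initiation, we use simulated personalization (F1) as the independent variable".
- Weeks 6 and 12: "For week 6 and 12, we use mid-treatment expectations focused contact (F2), as well as the interaction between F1 and F2 as independent variables".
- Covariates throughout: "All ANCOVA models will include age and baseline symptom severity as covariates".
- Reporting: "We will report marginal means for each factor level of the main factors and means for each treatment arm".

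No sentence places F1 as a main effect in the week 6 or week 12 model. Yet the first item under Objectives {7} is to "determine whether framing the IMI as personalized enhances initial expectations and amplifies treatment effects compared to standard framing". The section on the choice of comparators {6b} asks whether framing and contact together "contributes to the treatment outcome at 3, 6, and 12 weeks after randomization". Research Question 1 in {20a} names the same three time points for both factors. The section on strengths and limitations presents the factorial design as able to show each factor's own effect as well as their interaction.

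**The concern.** An interaction term has its usual meaning only when both of its main effects are in the model. Leave one out, and what the remaining product terms estimate depends on how the factors are coded. The article does not state the coding.

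Week 6 is the post-treatment assessment and part of the primary outcome. Two things are at stake there. Framing might get no estimate, or a biased one, although it is the first objective. And a framing effect that is the same in every contact arm could be reported as framing and contact interacting. In a proof-of-concept study meant to inform later trials, that would mislead the next design.

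**Working it through.** **Inputs from the protocol article.** A 2×3 design with equal allocation. Sample size {14} gives 100 analysable participants per cell, and 120 recruited per arm with 20% dropout, which leaves 120 × 0.80 = 96. I use 96 and 100 as the range.

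**The plan's own figure.** Sample size {14} gives about 200 participants for one two-cell comparison at d = 0.35, one-tailed alpha 0.05 and power 0.80. The normal approximation gives 101 per cell (202) and the exact t calculation 102 per cell (204), so the figure reproduces. It applies to any two cells, with framing and contact combined as the example. It is not a stated framing effect and does not settle this point.

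**Assumptions, not in the documents.** A framing effect d that is equal in all three contact arms, no contact effect, no true interaction, SD 1, no covariates, two-sided alpha 0.05, and d = 0.20, 0.25 or 0.35.

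**What the listed terms fit when framing lowers the score by 0.35 in every arm**

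| Coding of F2 + F1×F2 | Fitted framing difference, by contact arm (none, supportive, expectation) | Marginal framing difference |
|---|---|---|
| Sum-to-zero products, 2 df | 0, 0, 0 | 0.00 |
| 0/1 products, no contact as reference, 2 df | 0, 0.35, 0.35 | (0 + 0.35 + 0.35)/3 = 0.23 |
| Software expansion, 3 df | 0.35, 0.35, 0.35 | 0.35 |
| F1 + F2 + F1×F2 (full factorial) | 0.35, 0.35, 0.35 | 0.35 |

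Under sum-to-zero coding the framing effect goes into the residual. Under 0/1 coding both interaction coefficients take the full size of the framing effect. The 3-df expansion fits all six cell means and is the full factorial written differently, but its F1×F2 term is a joint test of three simple framing effects.

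**Noncentrality of the test labelled interaction, n per cell**

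- 3-df expansion: λ = 3 × (n/2) × d². At n = 96, d = 0.25: 3 × 48 × 0.0625 = 9.0.
- 0/1 products: λ ≈ 2 × (n/2) × d², because only two arms carry the term. At n = 96, d = 0.25: 2 × 48 × 0.0625 = 6.0.
- Sum-to-zero products and the full factorial: λ = 0.

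**Rejection rates for the test labelled interaction, with no true interaction** (noncentral F)

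| d | n per cell | 3-df expansion | 0/1 products |
|---|---|---|---|
| 0.20 | 96 | 50% | 40% |
| 0.20 | 100 | 52% | 41% |
| 0.25 | 96 | 71% | 58% |
| 0.35 | 96 | 95% | 87% |
| 0.35 | 100 | 96% | 88% |

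Simulation at 100 per cell (3,000 runs) agrees: 52.1% and 41.1% at d = 0.20, and 95.8% and 87.5% at d = 0.35. In the same runs the sum-to-zero version rejected in 4.6% and 3.9%, and the 2-df interaction test of the full factorial in 4.7% and 4.4%. At d = 0 every version stayed near 5%.

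**With F1 in the model.** The simulated power for the framing main effect at 100 per cell was 68% at d = 0.20 and 99% at d = 0.35.

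**The case against.** The strongest defence is that the surrounding text implies F1. A factorial ANCOVA conventionally carries its main effects. The two time-point sentences can be read cumulatively: F1 alone at week 3, because only framing has been delivered, then F2 and the interaction added later. Marginal means for the main factors, in the plural, presuppose F1. The article also promises an updated analysis plan before the Research Question 1 analysis. All this makes a drafting omission likely, and I accept that. It does not cure the sentence, because the term list is explicit and contradicts the reporting plan beside it. The updated plan is announced for issues that cannot yet be foreseen, and this one can.

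Two stronger readings are tempting. A reader might infer that the trial would have no valid test of framing after week 3. That fails for the 3-df expansion: cell means, marginal means and the F1 contrast are all recoverable, and only the interaction label misleads. A reader might also infer that a false interaction is to be expected. That fails for sum-to-zero coding, where the error rate stays nominal and the loss is an unestimated framing effect.

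It is also fair to say that the uniform effects are assumptions, that 0.35 is the protocol's figure for two cells and not for framing alone, and that the main analysis uses multiple imputation and not complete cases. The planned arm means would help readers see a uniform effect, provided they are taken from the data or from a model that fits all six cells.

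**Conclusion.** The point holds as an error in the stated primary-outcome model, probably one of drafting. As written, the week 6 and week 12 model omits the effect that the first objective asks for, and the meaning of its interaction test depends on a coding that the article does not give. Each of the three codings has a defect: no framing estimate, a biased estimate with a contaminated interaction test, or a valid framing contrast with a contaminated interaction test. The false-interaction rates of about 40 to 52% (d = 0.20) and 87 to 96% (d = 0.35) apply only to the last two codings, and only if framing works equally in all contact arms. They show what the literal model could do; they do not forecast the trial's result. The design and sample size are not affected.

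**What to change.** In {20a}, state the week 6 and week 12 model as F1 + F2 + F1×F2 + age + baseline severity. Test the interaction on 2 df. Use sum-to-zero contrasts, so that the F1 term is the framing difference averaged over the contact levels, and report that marginal difference at both time points. Carry the same wording into the updated analysis plan, since {20a} applies the method to the continuous secondary outcomes as well.

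The cost is one sentence and at most 1 degree of freedom (none compared with the 3-df expansion). Recruitment is expected to run until mid-2027 and no interim analysis is planned, so the change can be made before any outcome analysis.

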	**Study period**										
	**Enrollment**	**Baseline**	**Allocation**	**Post-allocation**							
**Timepoint****	*−t*_*1*_	*t*_*0*_	**0**	*Week 1 (t*_1_**)**	*Week 2 (t*_*2*_**)**	*Week 3 (t*_*3*_*)*	*Week 4 (t*_*4*_*)*	*Week 5 (t*_*5*_*)*	*Week 6 (t*_*6*_*)*	*Week 12 (t*_*7*_*)*	*Other*
Enrollment:											
Eligibility screen	X										
Informed consent	X										
Allocation			X								
Interventions:											
Simulated Personalization				X							
Personal Contact						X					
IMI modules				X	X	X	X	X	X		
Assessments:											
Sociodemographics	X	X									
Anxiety and Depression State and Trait (STADI)		X							X		
Expectations (TEX-Q)		X									
Subjective Stress (PSS-10)		X									
Somatosensory Amplification (SSAS)		X									
Desire for Relief (self-drafted)		X									
Acceptance (UTAUT)		X									
Depression (BDI-II)	X					X			X	X	
Depression (PHQ-9)		X		X	X	X	X	X	X	X	
Functioning (WSAS)		X							X		
Disability (PDI)		X							X		
Menopausal Symptoms (MRS)		X							X	X	
Depression gender-sensitive (GSDS)		X							X		
Personality (BFI-10)		X									
Goal Attainment (GAS)									X		
Negative Effects (INEP-ON)									X		
Usability (RAD									X		
Satisfaction with Treatment (CSQ-8)									X		
Expectations (GEEE)		X		X	X	X	X	X	X		
Prior Experiences (GEEE)		X									
Treatment Effects (GEEE)									X	X	
Session Fit (self-drafted)				X	X	X	X	X	X		
Self-Efficacy (ASKU)				X	X	X	X	X	X		
Working Alliance (WAI-I)				X	X	X	X	X	X		
Subjective Adherence (self-drafted)				X	X	X	X	X	X		
Warmth & Competence of Telephone Contact (SCM)											X
Warmth & Competence of App (SCM)						X			X		

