### Sample size {14}

To depict a clinically meaningful effect size of *d* = 0.35 between two arbitrary cells (e.g., personalized framing and expectation-optimizing contact vs. standard framing and no contact) in this proof-of-concept study, with an alpha of 0.05 and power of 0.80 (one-tailed, uncontrolled for multiplicity), an overall sample size of approximately 200 is needed according to G*Power [14]. The resulting sample of *N* = 600 (*n* = 100 per cell) should be sufficiently large to depict trends and inform future confirmatory trials. To consider a dropout rate of 20% per arm, we aim to recruit *N* = 720 patients (120 per treatment arm). We will include data assessed before starting the intervention as covariates to increase power.

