### Methods for additional analyses (e.g., subgroup analyses) {20b}

Beyond the question of whether and how these expectation-modulating strategies modulate treatment effects, we aim to explore the underlying mechanism. The following sub-questions are addressed:
Sub-question 1: *How do expectations and depressive symptoms evolve?*We plan to compute variants of pattern-mixture models using the weekly symptom and expectation ratings as outcomes to explore whether symptoms of depression and expectations evolve differently over time. The study group is either considered by a dummy coding variable or in the form of a multi-group model. Missing data will be treated under the MAR assumption.Sub-question 2: Does simulated personalization enhance initial treatment expectations?To answer sub-question 2, a similar ANCOVA model described above, but using the baseline expectation as a covariate, will be used to explore differences in expectation at t1.Sub-question 3: Which variables moderate or mediate the expectation-modulating interventions?Regression models considering interactions between the treatment group and baseline variables will be computed. Mediator analysis will be conducted. This analysis is highly explorative. The qualitative interviews about change mechanisms will be recorded, transcribed, and analyzed using qualitative content analysis by trained staff, with an appropriate review of the assessment quality (inter-rater reliability).

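### The covariates named for the ANCOVAs do not secure adjustment of each secondary outcome for its own baseline, which costs precision

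*Protocol article*

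**What the plan says.** Four statements in the protocol article bear on this.

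- **Statistical methods {20a}, covariates:** "All ANCOVA models will include age and baseline symptom severity as covariates".
- **Statistical methods {20a}, secondary outcomes:** "We will apply the same method for all other continuous secondary outcome measures available at the respective measurement occasions".
- **Additional analyses {20b}, sub-question 2:** differences in expectation at t1 are examined with "a similar ANCOVA model described above, but using the baseline expectation as a covariate".
- **Sample size {14}:** "We will include data assessed before starting the intervention as covariates to increase power". No covariates are listed there.

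Table 2 shows which outcomes have a baseline.

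- PHQ-9, STADI, WSAS, PDI, MRS and GSDS are all marked at t0 and again at week 6. PHQ-9 and MRS are also marked at week 12.
- INEP-ON, CSQ-8, usability and goal attainment are marked at week 6 only, so they have no baseline.
- The pre-treatment BDI-II is taken at enrollment.

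**The concern.** When an outcome is measured before treatment, that measurement is usually its best single predictor. Leaving it out of the ANCOVA leaves explainable variance in the residual and widens every interval for that outcome. The plan names two covariates for all models and passes them on unchanged. It then departs from them for expectation, which suggests that the default model does not contain the outcome's own baseline.

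The phrase for baseline severity is also undefined. It could mean the enrollment BDI-II in every model, or the baseline of whichever symptom scale is being analysed. For a functioning or disability scale the second reading is hard to sustain. Two analysts could fit different models from the same text. What is at stake is precision for the secondary outcomes and a single, fixed specification.

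**Working it through.** **1. The plan's own figure.** The sample size section gives about 200 for two cells at d = 0.35, one-tailed alpha 0.05 and power 0.80.

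- Normal approximation: n per cell = 2(1.645 + 0.842)²/0.35² = 100.9, so 101 per cell and 202 in total.
- Exact noncentral t: 102 per cell and 204 in total.

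The figure reproduces. It assumes no covariates, so the choice of covariates does not make it wrong.

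**2. Gain from the own baseline.** Let a = correlation of baseline BDI-II with the outcome, b = correlation of the own baseline with the outcome, and c = correlation of the two baselines.

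- Residual variance with BDI-II alone: 1 − a².
- Residual variance with both: 1 − (a² + b² − 2abc)/(1 − c²).
- Standard error ratio: the square root of the second divided by the first.

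Age is left out for simplicity. **All correlations are assumptions, because the documents give none.** Baseline BDI-II stays in the model, so the gain shown is what the own baseline adds to it. Power is illustrative: 100 per cell, d = 0.35, one-sided 0.05.

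| a / b / c | Residual variance, BDI-II only | Residual variance, both | SE ratio | SE reduction | Power |
|---|---|---|---|---|---|
| 0.45 / 0.5 / 0.7 | 0.797 | 0.730 | 0.957 | 4% | 0.870 to 0.895 |
| 0.5 / 0.6 / 0.8 | 0.750 | 0.639 | 0.923 | 8% | 0.887 to 0.927 |
| 0.3 / 0.5 / 0.4 | 0.910 | 0.738 | 0.901 | 10% | 0.829 to 0.892 |
| 0.2 / 0.5 / 0.3 | 0.960 | 0.747 | 0.882 | 12% | 0.811 to 0.888 |
| 0.4 / 0.6 / 0.5 | 0.840 | 0.627 | 0.864 | 14% | 0.854 to 0.931 |
| 0.3 / 0.7 / 0.4 | 0.910 | 0.510 | 0.748 | 25% | 0.829 to 0.966 |

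Worked row, 0.4 / 0.6 / 0.5: (0.16 + 0.36 − 0.24)/0.75 = 0.373. The residual variance is 0.627, and √(0.627/0.84) = 0.864.

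The first two rows are those where the two baselines overlap strongly, as one might expect for another depression scale such as PHQ-9. The gain is larger where the overlap is weaker, which is more plausible for WSAS or PDI.

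**3. Week-3 BDI-II for the call contrasts.** The week-3 model contains framing (F1) alone: "To explore the difference in depressive symptoms 3 weeks after treatment initiation, we use simulated personalization (F1) as the independent variable". The later models add the call: "For week 6 and 12, we use mid-treatment expectations focused contact (F2), as well as the interaction between F1 and F2 as independent variables". The plan therefore treats week 3 as preceding any effect of the call (F2), and the week-3 score might look like a further unused covariate. A large-sample simulation shows the limit of that idea. It assumed that F1 shifts week 3 by −0.2, that week 3 carries over with slope 0.6, that F1 has a further direct effect of −0.1, and that the call effect is −0.2.

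- Without week 3, the F1 coefficient is −0.22, which matches −0.1 + 0.6 × (−0.2).
- With week 3, the F1 coefficient is −0.10.
- The call contrast is −0.20 in both models.

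Week 3 lies on the path from F1 to the outcome and cannot join the shared factorial model without removing part of the F1 effect.

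**The case against.** The strongest reply is that the plan does not exclude own baselines.

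- The text says models will *include* the two covariates; it never says they are the only ones.
- The sample size section commits to pre-intervention covariates in general.
- For PHQ-9, STADI or GSDS, baseline symptom severity can fairly be read as the scale's own baseline.
- An updated analysis plan is promised before the first research question is analysed.
- Within-treatment covariates already enter the imputation.

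Much of this stands. A reader might infer that the plan adjusts solely for two covariates and discards every secondary outcome's baseline. The wording does not support that, and four secondary measures have no baseline to use.

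It does not remove the point. The general sentence on covariates names none, while the section that specifies the models names two. The contrast drawn for expectation points away from own-baseline adjustment by default. The ambiguity helps symptom scales but not WSAS or PDI. The promised update is meant for matters that cannot be foreseen, and covariates can be. Covariates in the imputation model do not by themselves adjust the ANCOVA.

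A reader might also infer that leaving week-3 BDI-II out of the call contrasts is an error. The documents do not support that either. Adjusting for pre-randomization covariates is a standard choice, and week-3 BDI-II is measured after randomization and can be affected by F1. Table 2 places it in the same week as the call without giving an order. Making the call wait for the questionnaire could delay or withhold a randomized intervention, which would work against the stated aim of estimating the effect if it is received.

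**Conclusion.** The point holds as one of efficiency and clarity. The plan names age and baseline symptom severity for all ANCOVAs and does not secure own-baseline adjustment for secondary outcomes that have a t0 value. This is clear for WSAS and PDI. For PHQ-9, STADI, MRS and GSDS it depends on how baseline symptom severity is read. Under the assumed correlations, the own baseline would lower the standard error by about 4% to 25%, with the small gains where it overlaps strongly with BDI-II. The direction holds in every case tried; the size rests entirely on those assumptions.

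Nothing here is biased or invalid, and the stated sample size is unaffected. The use of week-3 BDI-II in the call contrasts is a debatable refinement and not part of the finding.

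**What to change.** In the statistical methods section, state that every continuous secondary outcome with a t0 measurement is adjusted for its own baseline in addition to baseline BDI-II and age. State that outcomes without a t0 value (INEP-ON, CSQ-8, usability, goal attainment) keep the current covariates. Define baseline symptom severity as a named scale and time point. Name the same covariates in the sample size section, and reword sub-question 2 so that own-baseline adjustment is the rule and not the exception. The cost is a few sentences; no new data are needed.

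Optional only: where timestamps show that the t3 BDI-II preceded the call, a supplementary model for the F2 contrasts may add it, with F1 estimated from the model without it. This means a second model to report and imputation of missing week-3 values. Delivery of the call should not be made conditional on completing the questionnaire.
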